## **Abstract**

**Background:** Low and middle-income countries (LMICs) hold the majority of disease burden attributed to major depressive disorder (MDD). Despite this, there remains a substantial gap for access to evidence-based treatments for MDD in LMICs like Pakistan. Measurement-based care (MBC) incorporates systematic administration of validated outcome measures to guide treatment decision making and is considered a low-cost approach to optimise better clinical outcomes for individuals with MDD but there is a paucity of evidence on the efficacy of MBC in LMICs.

**Methods:** This protocol highlights a randomized trial which will include Pakistani outpatients with moderate to severe major depression. Participants will be randomised to either MBC (guided by schedule), or standard treatment (guided by clinicians' judgement), and will be prescribed with paroxetine (10–60mg/day) or mirtazapine (7.5–45mg/day) for 24 weeks. Outcomes will be evaluated by raters blind to study protocol and treatment.

**Discussion:** With increasing evidence from high-income settings supporting the effectiveness of MBC for MDD, it is now necessary to explore its feasibility, utility, and efficacy in low-resource settings. The results of the proposed trial could inform the development of a low-cost and scalable approach to efficiently optimise outcomes for individuals with MDD in Pakistan.

**Keywords:** Measurement-based care, Treatment guidelines, Depression, Major depressive disorder, Antidepressant treatment

**Trial registration:** NCT05431374

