### **Study Intervention and Procedure**

After providing informed consent, eligible patients will enter a one-week washout phase to eliminate any effects of psychotropic medications previously taken. After washout week, the patients will be assigned to treatment arms based on randomization schedule, where they will receive either **open-label paroxetine**

(10–50mg/day) or open-label mirtazapine (7.5–45mg/day). All patients will be followed for 24-weeks after randomization. This dosage range is recommended by the US Food and Drug Authority (*Paxil - Highlights of Prescribing Medication*, 2022; *Remeron -Highlights of Prescribing Medication*, 2022). Paroxetine is a commonly prescribed antidepressant, working as a selective serotonin reuptake inhibitor, while Mirtazapine, which works as an alpha-2 antagonist, has a different mechanism of action. Similar to the Guo et. al study (Guo et al., 2015), the decision about the prescription of drug and dosage will be made by the treating psychiatrists/GP. Depending on the duration of prescribed dosage, symptoms and side effects, the psychiatrist/GP will make adjustments. In case of intolerability or inefficacy, one medication change between paroxetine and mirtazapine will be allowed. Short-acting benzodiazepines, prescribed occasionally for agitation, anxiety, and insomnia, will be permitted, as well as any other medications not affecting the CNS.

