### ***Measurement-based Care***

At every outpatient visit, patient’s feedback will be recorded through the 16-item Quick Inventory of Depressive Symptomatology–Self-Report (QIDS-SR) (Rush et al., 2003) and the Frequency, Intensity, and Burden of Side Effects Rating scale (FIBSER) (Wisniewski et al., 2006). The QIDS-SR is used to measure depressive symptoms in the past one week, with higher scores indicating higher severity (Rush et al., 2003). FIBSER is completed by the patient to report antidepressant side effects on the domains of frequency, intensity, and burden (Wisniewski et al., 2006). A total score >4 is indicative of current treatment being unsuitable and requires revision to dosage/medication (Trivedi, 2009).

The patient’s responses on these self-report measures will inform and guide physician’s decisions. Following a stepwise approach, the treatment schedule will outline the dosage adjustment, and medication changes needed to mitigate the side effects, and promote therapeutic benefit for each patient. Originally driven from the STAR\*D project ([www.star-d.org](http://www.star-d.org)), the treatment schedule used by the Guo et. al. (2015) study (Guo et al., 2015) will facilitate the treatment schedule (Table 1), for this study. However, the starting dosage has been modified following a discussion with the stakeholders, which highlighted patient preference for slower dose titration when initiating preference. Treating physicians will undergo a two-day training to get acquainted with use of MBC schedule. Moreover, an independent research coordinator will be designated at each site to compare the physician’s clinical notes against the MBC treatment guidelines to ensure compliance and standardization. In case of any deviation from the MBC schedule, the physician will be notified and asked to make necessary treatment amendments.

*Table 1. The Measurement-Based Care Schedule*

| Time Point and Measure  | Clinical Status  | Treatment Plan                                                         |                                                                       |
|-------------------------|------------------|------------------------------------------------------------------------|-----------------------------------------------------------------------|
|                         |                  | Paroxetine                                                             | Mirtazapine                                                           |

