|                         | SEs intolerable  | Continue current dose and address SEs, or switch to mirtazapine        | Continue current dose and address SEs, or switch to paroxetine        |
| QIDS-SR score, $\geq 9$ | Nonresponse      | Increase to 40 mg/day                                                  | Increase to 45 mg/day or switch to paroxetine                         |
|                         | SEs intolerable  | Switch to mirtazapine                                                  | Switch to paroxetine                                                  |
| Week 8           |                  |                                                                        |                                                                       |
| QIDS-SR score, $\leq 5$ | Remission        | Continue current dose                                                  | Continue current dose                                                 |
| QIDS-SR score, 6–8      | Partial response | Continue current dose or consider increasing to 50 mg/day              | Continue current dose or consider increasing to 45 mg/day             |
|                         | SEs intolerable  | Switch to mirtazapine                                                  | Switch to paroxetine                                                  |
| QIDS-SR score, $\geq 9$ | Nonresponse      | Switch to mirtazapine                                                  | Switch to paroxetine                                                  |
|                         | SEs intolerable  | Switch to mirtazapine                                                  | Switch to paroxetine                                                  |
| Week 10          |                  |                                                                        |                                                                       |
| QIDS-SR score, $\leq 5$ | Remission        | Continue current dose                                                  | Continue current dose                                                 |
| QIDS-SR score, 6–8      | Partial response | Continue current dose or consider increasing to 60 mg/day              | Continue current dose or consider switch to paroxetine                |
|                         | SEs intolerable  | Switch to mirtazapine                                                  | Switch to paroxetine                                                  |

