| QIDS-SR score, $\geq 9$ | Nonresponse      | Switch to mirtazapine                                                  | Switch to paroxetine                                                  |
|                         | SEs intolerable  | Switch to mirtazapine                                                  | Switch to paroxetine                                                  |
| Week 12          |                  |                                                                        |                                                                       |
| QIDS-SR score, $\leq 5$ | Remission        | Continue current dose and follow up                                    | Continue current dose and follow up                                   |
| QIDS-SR score, 6–8      | Partial response | Continue current dose and follow up, or consider switch to mirtazapine | Continue current dose and follow up, or consider switch to paroxetine |
|                         | SEs intolerable  | Switch to mirtazapine                                                  | Switch to paroxetine                                                  |

| Time Point and Measure  | Clinical Status | Treatment Plan        |                      |
|-------------------------|-----------------|-----------------------|----------------------|
|                         |                 | Paroxetine            | Mirtazapine          |
| QIDS-SR score, $\geq 9$ | Nonresponse     | Switch to mirtazapine | Switch to paroxetine |
|                         | SEs intolerable | Switch to mirtazapine | Switch to paroxetine |

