We do not anticipate any major risks related to the intervention. However, we acknowledge that potentially vulnerable people with mental illness will be participating in the trial. Some topics discussed or questions asked in the sessions/assessments may cause distress, and in such instances, appropriate support will be provided. We will map available mental health resources ensuring pathways to care. The research team has considerable clinical and research experience, including the management of difficult situations arising in research interventions and interviews. In case participant recruited to this study experience active suicidal ideation or subsequently identified as needing more intensive treatment will be appropriately referred for psychiatric evaluation and treatment. Patients will be removed from the study if they report suicidal attempt, became pregnant, developed a severe medical condition, or suffered from newly emerging side effects that they find intolerable and that could not be managed. Patients who will be removed from the study will receive antidepressant treatment as appropriate as part of clinical care. Research staff will be provided with regular supervision throughout the duration of the project. We already have study protocols in place that include details about how to manage difficult situations arising in research, safety and lone working arrangements. In the event of any study-related injury or adverse event, intervention and treatment will be available from medical staff. Any adverse events will be reported to the REB within the required timeframe.

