### 3.2. Statistical Analyses

A treatment-blind statistician will analyze the data after completion of follow-ups for all recruited participants using SPSS for Windows, version 20.0 (IBMCorp., Armonk, N.Y.).

Like the Guo et al. (2015) trial, we will use independent-sample t-tests, Mann-Whitney U tests, and chi-square tests, to compare sociodemographic and clinical characteristics, discontinuation, response and remission rates, and side effects as appropriate. Full intent-to-treat analyses will be carried out to determine all-cause discontinuation. Estimated time from randomization to response and remission will be calculated using Kaplan-Meier survival analyses, and a comparative analysis will be facilitated using the Cox proportional hazards regression model. Analysis of covariance will be used to compare the changes in HDRS scores between the two groups. Additional subgroup analysis might be carried out to understand group-differences due to age, gender, duration of illness, and number of previous episodes. The significance threshold will be  $p < 0.05$  (two-tailed) for all analyses.

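### The protocol allows one drug change, but from week 8 Table 1 offers nonresponders only a switch, with no rule for a patient already switched; the paroxetine ceiling is also inconsistent (50 or 60 mg/day)

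*Combined protocol and SAP*

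**What the plan says.** The protocol's Study Intervention and Procedure section covers both arms. It states: "In case of intolerability or inefficacy, one medication change between paroxetine and mirtazapine will be allowed". It gives paroxetine as 10–50 mg/day and adds "This dosage range is recommended by the US Food and Drug Authority".

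Table 1, under Measurement-based Care, sets the plan for the MBC arm by visit, QIDS-SR score, side-effect status and drug. For QIDS-SR ≥9 at weeks 8, 10 and 12 the paroxetine and mirtazapine columns read "Switch to mirtazapine | Switch to paroxetine", whether or not side effects are tolerable. The same entry stands for intolerable side effects at QIDS-SR 6–8 at those weeks. The same section has a coordinator check clinical notes against the schedule: "In case of any deviation from the MBC schedule, the physician will be notified and asked to make necessary treatment amendments".

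On dose, the Abstract says patients "will be prescribed with paroxetine (10–60mg/day) or mirtazapine (7.5–45mg/day) for 24 weeks", and the week 10 partial-response cell for paroxetine reads "Continue current dose or consider increasing to 60 mg/day".

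SAP section 3.2 lists comparisons of "discontinuation, response and remission rates, and side effects as appropriate", but no report of drug changes.

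**The concern.** A physician treating an MBC patient who has already switched and scores ≥9 at week 10 faces two texts that point different ways. Following Table 1 by study week and current drug exceeds the limit. It also returns a patient switched at week 8 to the first drug after two weeks on the second, which resembles the rapid changeovers that the protocol's Introduction criticises. Keeping to the limit departs from the cell's literal wording, and the coordinator may ask for that to be corrected.

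What is at stake is the definition of the intervention. MBC is the arm guided by a schedule, and standard care is the arm guided by clinical judgement. For patients who do poorly on the second drug, the schedule either conflicts with the limit or falls silent. Without a report of drug changes, a reader of the results could not tell which text was followed. The replicated trial did report treatment adjustments by arm (44 against 23, cited in the Introduction).

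**Working it through.** **Inputs.** The limit of one change (Study Intervention and Procedure) and Table 1 for weeks 4, 6, 8, 10 and 12. Each week has 5 rows (remission; partial response; QIDS-SR 6–8 with intolerable side effects; ≥9 nonresponse; ≥9 with intolerable side effects) and 2 drug columns, so 5 × 5 × 2 = 50 cells.

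**Cell count.**

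| Week | Switch only | Switch optional | No switch |
|---|---|---|---|
| 4 | 2 | 4 | 4 |
| 6 | 2 | 3 | 5 |
| 8 | 6 | 0 | 4 |
| 10 | 6 | 1 | 3 |
| 12 | 6 | 2 | 2 |
| Total | 22 | 10 | 18 |

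No cell carries the limit. Of the 22 switch-only cells, 6 + 6 + 6 = 18 fall at weeks 8–12. The other 4 are the ≥9 rows with intolerable side effects at weeks 4 and 6.

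**Reading A: study week and current drug.** With tolerable side effects, the minimum number of switches over weeks 8, 10 and 12 equals the number of those visits with a score ≥9, because remission and partial response always permit continuing.

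- ≥9 at two of the three visits: at least 2 changes against 1 allowed.
- ≥9 at every visit from week 4, paroxetine start: 3 forced, plus optional switches at weeks 4 and 6, so 3–5.
- The same, mirtazapine start: 3 forced plus at most one earlier switch, so 3–4. A week 4 switch leads to the paroxetine week 6 cell, which allows only a dose increase.
- A patient who took an optional switch at week 4 or 6 exceeds the limit at the first later visit, from week 8, with a score ≥9.

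**Reading B: the limit prevails.** For a patient already switched, the 22 switch-only cells lose their instruction. The other 10 + 18 = 28 keep one, including every remission row and every partial-response row with tolerable side effects.

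**Reading C: columns mean the starting drug.** After a switch, the cell names the drug already being taken. There is no second change, but no further instruction either.

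**Reading D: weeks restart at each switch.** With tolerable side effects and no optional switch, forced switches fall at weeks 8 and 8 + 8 = 16, so there is one by week 12. An optional switch at week 4 makes study week 12 the new drug's week 8, giving two changes. With ≥9 and intolerable side effects throughout, each week 4 cell forces a switch, at study weeks 4, 8 and 12, giving three.

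**Paroxetine ceiling.** Study Intervention and Procedure: 50 mg/day. Abstract and Table 1, week 10: 60 mg/day. This does not depend on how the switch rule is read.

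**The case against.** The best defence is that a general limit stated for all patients bounds a table in a subsection, that the scores are described there as guiding the physician, and that physicians receive two days of training. This is a reasonable reading, and it stands to this extent: a reader might infer that Table 1 necessarily breaks the limit, and the documents do not support that. The breach follows under Reading A, and under some patterns of Reading D, but not under B or C.

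The defence does not close the matter. The text does not say that the limit prevails, and it does not say that the training covers it. Under B or C a patient doing poorly on the second drug lacks an instruction, while any departure from the schedule is to be corrected.

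A reader might also infer that nothing is left to follow after the one change. That is too strong: 28 of the 50 cells still apply. The Ethical and safety considerations section also provides referral for participants who need more intensive treatment, and removal for "newly emerging side effects that they find intolerable and that could not be managed". These are partial routes for someone failing both drugs, although Table 1 does not point to them.

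Finally, the protocol calls the trial a direct replication and takes its schedule from the earlier Chinese trial, mentioning only a modified starting dose. That is a fair argument against rebuilding the schedule after a switch with restarted titration and extra visits. A footnote is enough.

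**Conclusion.** The point holds as a conflict in the text that should be resolved. For QIDS-SR ≥9, and for intolerable side effects at 6–8, weeks 8, 10 and 12 of Table 1 give only a switch, against a limit of one change, and no rule of precedence is stated. The result is either a breach of the limit (at least 2 changes with ≥9 at two of these visits, under Reading A) or 22 cells, 18 of them from week 8, without an instruction for a patient already switched. The ceiling mismatch of 50 against 60 mg/day is a separate and explicit inconsistency.

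A reader might infer that the treatment comparison is biased, or that MBC patients were in fact allowed more switches than controls. The documents support neither. Randomisation and the primary time-to-event analysis are untouched, and any difference in switching allowance depends on which text sites followed. Nor do the documents show that 60 mg/day is unsafe: they show only that it exceeds the range the protocol itself describes as recommended.

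The share of patients affected and the effect on time to response or remission cannot be sized. For scale only, if the 120 patients divide equally, each 5% of the MBC arm is 0.05 × 60 = 3 patients.

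**What to change.** 1. **Precedence.** State in Study Intervention and Procedure, and in a footnote to Table 1, that each patient in either arm may change between the two drugs at most once and that this overrides every switch entry. After the one change, a switch entry means continuing at the highest tolerated dose and addressing side effects, with the referral and removal rules in Ethical and safety considerations applying. Coordinators check notes against the table with that limit.
2. **One paroxetine ceiling.** Use 50 mg/day throughout, as in Study Intervention and Procedure, and correct the Abstract and the week 10 cell.
3. **Reporting.** Add to SAP section 3.2 a descriptive table, by arm, of the number and timing of drug changes and the number of patients with more than one. The sources are the clinical notes that coordinators review in the MBC arm and the record of standard care that research staff keep.

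**Cost.** Items 1 and 2 need one amendment with ethics approval, a footnote and brief retraining. A patient who fails both drugs stays on the second unless referred or removed. Patients who might have reached 60 mg/day stop at 50, a small departure from the schedule Table 1 now gives. Item 3 costs one table. SAP section 3.1 speaks of interim analyses in the past tense, so treatment may already be complete; if it is, item 3 is the only part that still applies. The primary analysis does not change.

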### ***Measurement-based Care***

At every outpatient visit, patient’s feedback will be recorded through the 16-item Quick Inventory of Depressive Symptomatology–Self-Report (QIDS-SR) (Rush et al., 2003) and the Frequency, Intensity, and Burden of Side Effects Rating scale (FIBSER) (Wisniewski et al., 2006). The QIDS-SR is used to measure depressive symptoms in the past one week, with higher scores indicating higher severity (Rush et al., 2003). FIBSER is completed by the patient to report antidepressant side effects on the domains of frequency, intensity, and burden (Wisniewski et al., 2006). A total score >4 is indicative of current treatment being unsuitable and requires revision to dosage/medication (Trivedi, 2009).

The patient’s responses on these self-report measures will inform and guide physician’s decisions. Following a stepwise approach, the treatment schedule will outline the dosage adjustment, and medication changes needed to mitigate the side effects, and promote therapeutic benefit for each patient. Originally driven from the STAR\*D project ([www.star-d.org](http://www.star-d.org)), the treatment schedule used by the Guo et. al. (2015) study (Guo et al., 2015) will facilitate the treatment schedule (Table 1), for this study. However, the starting dosage has been modified following a discussion with the stakeholders, which highlighted patient preference for slower dose titration when initiating preference. Treating physicians will undergo a two-day training to get acquainted with use of MBC schedule. Moreover, an independent research coordinator will be designated at each site to compare the physician’s clinical notes against the MBC treatment guidelines to ensure compliance and standardization. In case of any deviation from the MBC schedule, the physician will be notified and asked to make necessary treatment amendments.

*Table 1. The Measurement-Based Care Schedule*

| Time Point and Measure  | Clinical Status  | Treatment Plan                                                         |                                                                       |
|-------------------------|------------------|------------------------------------------------------------------------|-----------------------------------------------------------------------|
|                         |                  | Paroxetine                                                             | Mirtazapine                                                           |
|                         |                  |                                                                        |                                                                       |
| Week 0           |                  | Start at 10 mg- 20 mg/day                                              | Start at 7.5 mg- 15mg/day, increase to 15 mg/day by week 1            |
| Week 2           |                  |                                                                        |                                                                       |
| Outpatient visit,       |                  | Increase or maintain dose at 20 mg/day                                 | Increase or maintain dose at 15 mg/day                                |
| Week 4           |                  |                                                                        |                                                                       |
| QIDS-SR score, $\leq 5$ | Remission        | Continue current dose                                                  | Continue current dose                                                 |
| QIDS-SR score, 6–8      | Partial response | Continue current dose or consider increasing to 30 mg/day              | Continue current dose or consider increasing to 45 mg/day             |
|                         | SEs intolerable  | Continue current dose and address SEs, or switch to mirtazapine        | Continue current dose and address SEs, or switch to paroxetine        |
| QIDS-SR score, $\geq 9$ | Nonresponse      | Increase to 30 mg/day or switch to mirtazapine                         | Increase to 45 mg/day or switch to paroxetine                         |
|                         | SEs intolerable  | Switch to mirtazapine                                                  | Switch to paroxetine                                                  |
| Week 6           |                  |                                                                        |                                                                       |
| QIDS-SR score, $\leq 5$ | Remission        | Continue current dose                                                  | Continue current dose                                                 |
| QIDS-SR score, 6–8      | Partial response | Continue current dose or consider increasing to 40 mg/day              | Continue current dose or consider increasing to 45 mg/day             |
|                         | SEs intolerable  | Continue current dose and address SEs, or switch to mirtazapine        | Continue current dose and address SEs, or switch to paroxetine        |
| QIDS-SR score, $\geq 9$ | Nonresponse      | Increase to 40 mg/day                                                  | Increase to 45 mg/day or switch to paroxetine                         |
|                         | SEs intolerable  | Switch to mirtazapine                                                  | Switch to paroxetine                                                  |
| Week 8           |                  |                                                                        |                                                                       |
| QIDS-SR score, $\leq 5$ | Remission        | Continue current dose                                                  | Continue current dose                                                 |
| QIDS-SR score, 6–8      | Partial response | Continue current dose or consider increasing to 50 mg/day              | Continue current dose or consider increasing to 45 mg/day             |
|                         | SEs intolerable  | Switch to mirtazapine                                                  | Switch to paroxetine                                                  |
| QIDS-SR score, $\geq 9$ | Nonresponse      | Switch to mirtazapine                                                  | Switch to paroxetine                                                  |
|                         | SEs intolerable  | Switch to mirtazapine                                                  | Switch to paroxetine                                                  |
| Week 10          |                  |                                                                        |                                                                       |
| QIDS-SR score, $\leq 5$ | Remission        | Continue current dose                                                  | Continue current dose                                                 |
| QIDS-SR score, 6–8      | Partial response | Continue current dose or consider increasing to 60 mg/day              | Continue current dose or consider switch to paroxetine                |
|                         | SEs intolerable  | Switch to mirtazapine                                                  | Switch to paroxetine                                                  |
| QIDS-SR score, $\geq 9$ | Nonresponse      | Switch to mirtazapine                                                  | Switch to paroxetine                                                  |
|                         | SEs intolerable  | Switch to mirtazapine                                                  | Switch to paroxetine                                                  |
| Week 12          |                  |                                                                        |                                                                       |
| QIDS-SR score, $\leq 5$ | Remission        | Continue current dose and follow up                                    | Continue current dose and follow up                                   |
| QIDS-SR score, 6–8      | Partial response | Continue current dose and follow up, or consider switch to mirtazapine | Continue current dose and follow up, or consider switch to paroxetine |
|                         | SEs intolerable  | Switch to mirtazapine                                                  | Switch to paroxetine                                                  |

| Time Point and Measure  | Clinical Status | Treatment Plan        |                      |
|-------------------------|-----------------|-----------------------|----------------------|
|                         |                 | Paroxetine            | Mirtazapine          |
| QIDS-SR score, $\geq 9$ | Nonresponse     | Switch to mirtazapine | Switch to paroxetine |
|                         | SEs intolerable | Switch to mirtazapine | Switch to paroxetine |

